## Methods/design

### Aims

Our aim is to perform a detailed evaluation of the effects of citrate on the coagulation and fibrinolysis pathways during CRRT. The primary objective is to determine changes in primary haemostasis, coagulation and fibrinolysis parameters from baseline within the patient’s systemic circulation and the CRRT circuit over the course of 72 h of regional anticoagulation with citrate. The outcomes are parameters reflecting the coagulation and fibrinolysis pathways (see below).

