### Sample size calculation

A formal sample size calculation was not possible due to lack of data in the literature. Following discussion with experts in the field, a sample size of 12 participants with complete data for 48–72 h was considered to be adequate to gain better understanding of coagulation and fibrinolysis during citrate based CRRT and to inform the design of future studies.

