#### During CRRT

At 12, 24, 36, 48 and 72 h after commencing CRRT, blood samples will be taken from the systemic circulation and from the CRRT circuit to measure the following parameters: FBC, PT, APTTr, fibrinogen, D-Dimers, thrombin generation assay, clot lysis and platelet function screening.

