### Statistical analysis

The baseline characteristics will be summarised using appropriate descriptive statistics [i.e. frequency (percentage) for categorical data and mean (standard deviation) or median (interquartile range) for continuous data]. All coagulation and fibrinolysis parameters at baseline will be summarised as means (standard deviation) unless the distribution is highlight skewed, in which case median values (interquartile range) will be used.

Average coagulation and fibrinolysis parameters at each time point, and the mean (standard deviation) of the difference relative to baseline will be presented. The evolution of parameters will also be illustrated graphically by plotting the mean (with 95% confidence interval) against time points. Trajectories of individual patients over time will be shown graphically. Separate figures will be used to summarise data obtained from bloods taken from the patient and that from the CRRT circuit.

Repeated measures analysis of variance (ANOVA) (one for each of the parameters obtained from patient’s bloods and separately for those from the circuit), will be used to further explore changes in parameters over time. Where CRRT ends before 72 h patients will not have measurements taken at 72 h. The ANOVA will therefore include all measurements up to 48 h (unless all patients have complete data to 72 h, in which case the final time point will also be included). If a main effect of time is identified, post-hoc comparisons will be carried out to determine where differences lie.

Coagulation and fibrinolysis parameters from the patients’ blood will be plotted against the corresponding value obtained from blood drawn from the CRRT circuit. The mean (standard deviation) of the differences will be calculated overall and at each time point and Bland-Altman limits of agreement calculated.

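### One missing 72 h sample removes every patient's 72 h value from the repeated-measures ANOVA, although the primary objective runs to 72 h

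*Protocol article*

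**What the plan says.** All references are to the protocol article.

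- **Aims.** The primary objective is change from baseline in the patient's circulation and in the circuit "over the course of 72 h of regional anticoagulation with citrate".
- **During CRRT.** The sampling schedule reaches the full horizon of the objective: "At 12, 24, 36, 48 and 72 h after commencing CRRT, blood samples will be taken from the systemic circulation and from the CRRT circuit". A baseline sample is taken just before CRRT starts.
- **Sample size calculation.** "A formal sample size calculation was not possible due to lack of data in the literature"; instead, after expert discussion, "a sample size of 12 participants with complete data for 48–72 h was considered to be adequate".
- **Statistical analysis.** Means at each time point, the mean and SD of the difference from baseline, plots of means with 95% confidence intervals and individual trajectories are all planned. None of these is cut at 48 h. A repeated-measures ANOVA for each parameter, separately for patient and circuit, "will be used to further explore changes in parameters over time". The section then notes that "Where CRRT ends before 72 h patients will not have measurements taken at 72 h" and concludes: "The ANOVA will therefore include all measurements up to 48 h (unless all patients have complete data to 72 h". Pairwise testing follows conditionally: "If a main effect of time is identified, post-hoc comparisons will be carried out to determine where differences lie".

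**The concern.** The window of the inferential analysis does not match the objective. The ANOVA, with its post-hoc comparisons, is the only planned test of change over time. Whether it reaches 72 h depends on the least complete patient in the study. The plan itself expects CRRT to end early in some patients, and the Withdrawal criteria section adds further reasons for sampling to stop (DIC, a systemic anticoagulant or antiplatelet agent, platelets or clotting factors).

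When the rule takes effect, 72 h measurements that were collected, assayed and paid for are left out of the test. With 12 patients there is little information to spare. The last interval, from 48 to 72 h, is the one that would show whether an early change persists or continues.

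**Working it through.** **Inputs from the article.** There are 12 participants. Samples are taken at baseline and at 12, 24, 36, 48 and 72 h. The ANOVA includes 72 h only if all patients are complete to 72 h. The figure of 12 carries no alpha, power, effect size or SD, so there is no calculation to reproduce.

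**Input not in the article.** The probability *p* that a patient has complete data to 72 h is not given. It is assumed here over the range 0.80 to 0.98, with patients independent of each other.

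**Step 1: chance that 72 h enters the ANOVA.** All 12 must be complete, so the chance is *p*^12.

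**Step 2: patients expected to have 72 h data.** This is 12*p*.

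**Step 3: 72 h values discarded when the rule takes effect.** Given that at least one patient is incomplete, the expected number of complete patients is (12*p* − 12*p*^12) / (1 − *p*^12).

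| Assumed *p* | *p*^12 | 12*p* | Expected 72 h values discarded if not all complete |
|---|---|---|---|
| 0.98 | 0.785 | 11.8 | (11.76 − 9.417) / 0.2153 = 10.9 |
| 0.95 | 0.540 | 11.4 | (11.40 − 6.484) / 0.4596 = 10.7 |
| 0.90 | 0.282 | 10.8 | (10.80 − 3.389) / 0.7176 = 10.3 |
| 0.80 | 0.069 | 9.6 | (9.60 − 0.825) / 0.9313 = 9.4 |

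**Step 4: break-even values.** An even chance that 72 h is included needs *p* = 0.5^(1/12) = 0.944. An 80% chance needs *p* = 0.8^(1/12) = 0.982. The chance falls below 5% only when *p* is under 0.05^(1/12) = 0.779.

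Over the assumed range, therefore, when the rule removes 72 h it discards on average between 9 and 11 of 12 possible values.

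**The case against.** The strongest defence is that the study is descriptive and the ANOVA secondary. The abstract's aim is to describe, the design is an observational cohort, and the ANOVA is introduced as further exploration. Change from baseline at 72 h, with its SD, is presented unconditionally. This stands, and it limits the point: a reader might infer that the 72 h objective goes unanswered or that change from baseline is seen only after a significant overall test, but neither is so. Only the formal comparisons are conditional.

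The rule is also fixed in advance and turns on completeness, not on observed parameter values. A common 48 h window has the merit of keeping the same patients at every time. That is a reason to keep it as a supporting analysis, but not to discard observed 72 h data from the main one.

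Three stronger readings are tempting but are not supported:

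- *The ANOVA will almost never reach 72 h.* This depends on a completion rate that the article does not give. Entry requires an expected CRRT duration beyond 72 h, and at *p* = 0.95 the rule is met more often than not.
- *Any patient with one missing sample is lost.* The article does not state listwise deletion. Its sample size section defines the 12 as complete for at least 48 h, which matches the ANOVA window. The abstract speaks only of recruiting 12, so some loss before 48 h cannot be excluded, but handling of a single failed sample may sit in the full protocol or SAP.
- *The F test is anticonservative.* This presumes no correction for non-sphericity. The article does not say that, and such detail is commonly left to a SAP.

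Finally, a mixed model is not free of assumptions. Once CRRT has ended there is no circuit to sample, so a circuit value at 72 h is undefined and not merely unobserved. This objection stands and is taken into the fix.

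**Conclusion.** The point holds in a limited form. The stated all-or-nothing rule lets one incomplete patient remove all 72 h values from the only planned test of change over time, which conflicts with a 72 h objective and a scheduled 72 h sample. This is a rule written into the plan, not a detail left out of a condensed article.

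How often the rule takes effect is uncertain. With independent patients, 72 h is more likely than not to be excluded if per-patient completion is below about 94%, and more likely than not to be included above that. The consequence is confined to the exploratory inferential analysis, because the descriptive summaries still reach 72 h.

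**What to change.** Delete the condition that all patients must be complete to 72 h. Replace the ANOVA with a likelihood-based linear mixed model for each parameter, fitted separately to patient and circuit samples, with:

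- time as a categorical effect;
- a simple covariance structure that 12 patients can support;
- small-sample degrees of freedom;
- every available sample to 72 h.

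For the patient's blood, report the contrast of each time point with baseline, with a 95% confidence interval, whatever the overall test of time shows. Give the number of patients contributing at each time. Keep the 48 h common-window analysis as a sensitivity analysis.

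The cost is analysis wording only; no extra sampling is needed. The plan should state the downside. The 72 h estimate relies on data being missing at random, whereas early end of CRRT or withdrawal may be related to the coagulation outcomes. Circuit values do not exist after CRRT ends, so circuit results should be described as applying to patients still on CRRT.

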## Discussion

To our best knowledge, this is the first study that will provide a detailed description of clotting and fibrinolysis processes before CRRT and the effects of citrate on coagulation pathways, fibrinolysis and platelet function during CRRT.

The strengths of this project are:i)The project will provide data that are currently not available.ii)By using very tight inclusion and exclusion criteria we are minimising confounding influences as much as possible.iii)Serial blood samples will be taken from the systemic circulation and the CRRT circuit separately to differentiate between events in the patient and in the extracorporeal circuit.iv)The results have potential to inform the design of future exploratory studies and intervention trials aimed a prolonging circuit life during CRRT and preventing unplanned interruptions in treatment.

We are aware of potential limitations and risks of the project which we will eliminate as much as possible.i)As a result of very strict criteria for inclusion, exclusion and withdrawal and a relatively long sampling period, recruitment is likely to be slow.

It is possible that we identify medical problems through this research that may have implications for patients and their close relatives, for instance a genetic predisposition to clotting which was previously not known about. With approval by the Research Ethics Committee, we have put measures in place to make sure that affected patients and relatives will receive the necessary medical attention.

Depending on the findings of the study, we plan to incorporate the results into current guidelines and clinical practice and hope that premature filter clotting can be prevented and the delivery of CRRT improves.

## Abbreviations

ABW: actual body weight
AKI: Acute kidney injury
ANOVA: Repeated measures analysis of variance
APACHE: Acute Physiology and Chronic Health Evaluation
APCR: Resistance to activated protein C
APTTr: Activated partial thromboplastin time ratio
BMI: Body mass index
CRP: C-reactive protein
CRRT: Continuous renal replacement therapy
DAPTT: Dilute Activated Partial Thromboplastin Time (DAPTT)
DIC: Disseminated Intravascular Coagulation
DRVVT: Dilute Russell’s Viper Venom Time
DVT: Deep vein thrombosis
ELISA: Enzyme linked immunosobent assays
FBC: Full blood count
ICU: Intensive care unit
PT: Prothrombin time
SOFA: Sequential Organ Failure Assessment
TAT: Thrombin-antithrombin complexes
VWF: Von Willebrand factor
